## Abstract

Determining readiness for duty after mild traumatic brain injury (mTBI) is essential for the safety of service members and their unit. Currently, these decisions are primarily based on self-reported symptoms, objective measures that assess a single system, or standardized physical or cognitive tests that may be insensitive or lack ecological validity for warrior tasks. While significant technological advancements have been made in a variety of assessments of these individual systems, assessments of isolated tasks are neither diagnostically accurate nor representative of the demands imposed by daily life and military activities. Emerging evidence suggests that complex tasks, such as dual-task paradigms or turning, have utility in probing functional deficits after mTBI. Objective measures from turning tasks in single- or dual-task conditions, therefore, may be highly valuable for clinical assessments and return-to-duty decisions after mTBI. The goals of this study are to assess the diagnostic accuracy, predictive capacity, and responsiveness to rehabilitation of objective, dual-task turning measures within an mTBI population. These goals will be accomplished over two phases. Phase 1 will enroll civilians at three sites and active-duty service members at one site to examine the diagnostic accuracy and predictive capacity of dual-task turning outcomes. Phase 1 participants will complete a series of turning tasks while wearing inertial sensors and a battery of clinical questionnaires, neurocognitive testing, and standard clinical assessments of function. Phase 2 will enroll active-duty service members referred for rehabilitation from two military medical treatment facilities to investigate the responsiveness to rehabilitation of objective dual-task turning measures. Phase 2 participants will complete two assessments of turning while wearing inertial sensors: a baseline assessment prior to the first rehabilitation session and a post-rehabilitation assessment after the physical therapist determines the participant has completed his/her rehabilitation course. A variable selection procedure will then be implemented to determine the best task and outcome measure for return-to-duty decisions based on diagnostic accuracy, predictive capacity, and responsiveness to rehabilitation. Overall, the results of this study will provide guidance and potential new tools for clinical decisions in individuals with mTBI.

**Clinical Trial Registration**: clinicaltrials.gov, Identifier NCT03892291.

## Introduction

Determining readiness for duty after mild traumatic brain injury (mTBI) is essential for the safety of service members (SMs) and their units. Sensory, motor, and cognitive deficits such as delayed reaction time (1), imbalance (2), and poorer cognitive functioning (3, 4) can pose serious risks to individuals following mTBI. Athletes with a recent mTBI are 60 to 70% more likely to experience a musculoskeletal injury over the subsequent 12 months compared to teammates without a recent mTBI, despite having no obvious clinical impairment, suggesting that these individuals are not fully ready for competitive activity when medically cleared after their mTBI (5–10). In SMs with mTBI, lasting impairments can have more severe implications. The ability to perform warrior tasks and battle drills, such as moving under fire while maintaining situational awareness, reacting to contact, and establishing security, is a critical component of combat effectiveness and survival for the SMs and their unit (11, 12). Additionally, the unit's mission readiness depends on the health of every SM; withholding an SM from duty requires convincing justification that they pose a tangible risk to themselves or their unit. Thus, return-to-duty (RTD) decisions should be made using objective assessments that are sensitive to mTBI-related deficits and are associated with functional performance in theater.

Currently, RTD decisions are based on self-reported symptoms, objective measures that assess a single system, or standardized physical tests that lack ecological validity for warrior tasks or battle drills. Duty-readiness is primarily assessed using patient-reported symptoms (13–16) and through batteries of clinical tests designed to detect single-system impairments in isolated sensory, balance, or cognitive domains. Decisions that hinge on self-reported symptoms do not assess function (12), and it is unclear whether self-reported symptoms are associated with job performance decrements that would constitute a tangible risk to SMs or their units. While persistent symptoms have been associated with lower quality of life and community integration (17–19), the impact of symptoms on comprehensive, functional performance is poorly understood (20, 21). Recently, the rehabilitation community has recognized the need to measure a multifaceted battery of assessments to characterize mTBI recovery (22–24), but these batteries remain a compilation of single-domain clinical assessments and may not be representative of the demands imposed by daily life and military activities (12, 25–29). The majority of warrior tasks (urban assault, building breaching, movement to contact, etc.) require the constant integration of complex sensory stimuli (visual, vestibular, and proprioceptive) while under cognitive load during movement in extreme and varying physical conditions (30, 31).

While understudied in mTBI populations (32), ambulatory turning is a complex task that requires the simultaneous integration of various systems that can be impaired after mTBI. Safe and effective turning is dependent on multiple systems and sophisticated integration between vestibular, ocular, somatosensory, motor, and cognitive functioning (33–35) to achieve coordinated head and body reorientation (36, 37). During turning, dynamic shifts in the body-sensed gravitoinertial acceleration reference frame (38) and asymmetrical loadings (39) alter vestibular and proprioceptive sensory information, requiring dynamic reweighting of sensorimotor information and sophisticated oculomotor reflexes to stabilize spatial information (38). Multisegmental coordination between the head, trunk, pelvis, and feet is required during turning to reorient the body and to account for the centripetal force and the increased risk of slips (40, 41) caused by transverse loads (39, 42–44). Even in a non-athlete population, turning is a critical functional movement; people generally turn 800 to 1,000 times per day (45), and more than 40% of daily steps are non-straight (46).

Turning velocity and head–body coordination during activities with cognitive demands are critical to an SM's ability to safely and effectively scan and maneuver through operational environments. The ability to successfully acquire, aim, and hit a target is a critical warrior task that requires rapid and coordinated reorientation of the head and body (47). Further, performance of a military agility drill during standard agility tasks is largely influenced by the quality of turning (48). Combining turning tasks with realistic cognitive demands may better reflect functional performance (12, 49–51). The ability to do two tasks at once is theorized to require executive control as attention must be appropriately allocated to successfully perform both tasks. Individuals with mTBI and more severe acquired brain injury show difficulty when performing simultaneous motor and cognitive tasks (52), including decreased walking speed, increased variability, decreased stability (53), and an impaired ability to perceive and avoid obstacles when walking (54). Warfighter tasks require decision-making and intact cognitive and sensory function and are often performed in dynamic and stressful environments requiring elite physical abilities. Simultaneous and dynamic measurement of turning in combination with appropriate and ecologically relevant cognitive overlay may be a sensitive and reliable paradigm to assess real-world function in a standardized and measurable way.

Quantifying turning performance has traditionally been difficult in clinical settings, but recent advances in wearable sensors have enabled objective, robust, reliable, and sensitive assessments of turning performance in other clinical populations (45, 55–59). This project is designed to transition our previous research findings (8, 9, 21, 45, 55–59) into clinical settings for improved assessments after mTBI by evaluating objective dual-task (DT) turning measures for use as rehabilitative outcomes and as tools for RTD assessments. Therefore, the first goal of this study is to assess diagnostic accuracy—the added value of objective DT turning measures over standard clinical assessments. We hypothesize (a) that objective turning measures, performed in DT contexts, will improve the diagnostic accuracy relative to standard clinical assessments of physical function among people with mTBI and (b) that objective turning measures, performed in DT contexts, will be associated with impairments in International Classification of Functioning, Disability, and Health (ICF) model components, including body functions and structures, activities, and participation domains (60). The second goal of this study is to determine predictive capacity—if objective DT turning measures predict functional performance in civilian and military relevant tasks. We hypothesize that objective turning measures, performed in DT contexts and obtained in the clinic, will predict functional performance in (a) ecologically relevant civilian environments and in (b) ecologically relevant simulated high-demand battle drills. Our third goal in this study is to assess responsiveness to rehabilitation—the responsiveness of objective DT turning measures to standard vestibular rehabilitation in active-duty SMs with residual mTBI-related symptoms. We hypothesize that objective turning measures, performed in DT contexts, will measurably improve over the course of customary rehabilitation for SMs with mTBI-related residual symptoms.

## Methods/Design

This study has two phases: for Phase 1, participants will be recruited from the general civilian populations surrounding three sites [Oregon Health & Science University (OHSU), University of Utah (UU), Courage Kenny Research Center (CKRC)] and active-duty SMs at one site [Fort Sam Houston (FSH)] to address the first two goals of the study (diagnostic accuracy and predictive capacity). For Phase 2, participants will be recruited from active-duty SMs referred to military medical treatment facilities (Evans Army Community Hospital and Madigan Army Medical Center) for physical therapy following mTBI to address the third goal of the study (responsiveness to rehabilitation). This study has been registered on ClinicalTrials.gov (NCT03892291).

### Phase 1: Diagnostic Accuracy and Predictive Capacity of Turning Measures

#### Participants

Phase 1 will include approximately 50 civilians with persistent symptoms from mTBI, 50 civilian healthy controls, and 40 active-duty SM healthy controls. Three non-military sites (OHSU, UU, CKRC) will test civilians. A fourth military site (FSH) will enroll and test 40 active-duty SM healthy controls across a range of military experience and ability levels.

#### Inclusion and Exclusion Criteria

Participants may be active duty (at FSH), veterans, or nonveterans and must (1) have a diagnosis of mTBI based on Veterans Affairs/Department of Defense (VA/DoD) criteria (61, 62), (2) be between 18 and 50 years old, and (3) be outside of the acute stage (>3 weeks postconcussion) according to the VA/DoD clinical practice guidelines (63) but within 3 years of their most recent mTBI and still reporting symptoms. Control participants must have no history of mTBI or be more than 7 years removed from their most recent mTBI and no reported residual symptoms. All participants must (1) not have had or currently have any other injury, medical, or neurological illness that could potentially explain balance deficits (e.g., central or peripheral nervous system disease, stroke, greater than mild TBI, lower extremity amputation, recent (<6 months) lower extremity or spine orthopedic injury requiring a profile); (2) meet criteria for moderate to severe substance-use disorder within the past month, as defined by *Diagnostic and Statistical Manual of Mental Disorders, Fifth Edition* (64); (3) display behavior that would significantly interfere with validity of data collection or safety during the study; (4) be in significant pain during the evaluation (7/10 by patient subjective report); (5) be a pregnant female (balance considerations); or (6) be unable to communicate in English.

#### Assessment Procedures

All assessment procedures for Phase 1 will occur in a single session. Potential participants will be screened for eligibility prior to scheduling their assessment and their arrival at the clinic. Upon arrival at the clinic, study team personnel will review the study procedures and obtain informed written consent from the participant. All participants will be assessed using a battery of assessments including self-reported questionnaires, computerized neurocognition, single-task and DT turning, ecologically relevant mobility tests, clinical mobility tests, and vestibular–ocular motor screening. All procedures have been approved by local institutional review boards and the US Army Medical Research and Materiel Command, Office of Research Protections, Human Research Protection Office.

#### Primary Outcome Measures—Diagnostic Accuracy

The primary outcome measures will be obtained through a series of clinical turning tasks (Table 1). Each participant will complete three prescribed clinical turning assessments in the laboratory while being measured with wearable sensors. The prescribed tests will involve a 1-min walk test between two lines on the ground marked 6 m apart (1MW), a modified Illinois Agility Test (mIAT) (65, 66), and a custom clinical turning course (CCTC) designed to mimic turns performed in daily life (21) (Figure 1). All participants will perform one block of turning tasks. Each block will consist of one 1MW, one mIAT, and one CCTC performed with no additional cognitive task, and one 1MW, one mIAT, and one CCTC performed with a simultaneous cognitive overlay. The cognitive overlay for the 1MW and the mIAT involves an 8-digit grid coordinate memorization task. The overlay for the CCTC involves monitoring and responding to keywords in a custom-developed simulated radio chatter task (28). A subset of participants will complete a second block of turning tasks to establish test–retest reliability and minimum detectable change.

**Table 1 T1:** Primary outcomes from objective turning tasks in phase 1.

	**Description**	**Purpose**
**Primary outcome**		
Peak lumbar turning speed (rad · s^−1^)^*^	Assesses the peak angular rate of the pelvis measured in the transverse plane	To assess whether the speed of reorientation changes after mTBI
**Other objective turning outcomes**		
Head turning speed (rad · s^−1^)^*^	Assesses the peak angular rate of the head measured in the transverse plane	To assess differences in the peak angular rate of superior body segments between people with mTBI and healthy controls
Upper trunk turning speed (rad · s^−1^)^*^	Assesses the peak angular rate of the upper trunk (sternum) measured in the transverse plane	
Head–body coordination timing (s)^*^	Assesses the time difference between peak angular velocity of the head and peak angular velocity of the trunk	To assess differences in head–body coordination during turning between people with mTBI and healthy controls
Peak head-pelvis angular displacement/RoM (°)	Assesses the peak angular displacement between the head and the trunk measured prior to or at the onset of trunk axial rotation when turning, measured in the transverse plane	
Head turn symmetry	Assesses the ratio of left-to-right head-turn velocity	

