#### Statistical Analysis

To evaluate the capability of objective, DT turning measures to discriminate between healthy controls and people with mTBI, we will construct receiver operating characteristic (ROC) curves using each objective turning outcome and clinical assessment of activity. The area under the ROC curve (AUC) will be calculated, and AUC confidence intervals will be generated through a bootstrapping procedure. We will compare the AUCs and confidence intervals between each objective turning measure and clinical assessment of activity using tests of equality and a 0.05 significance level with Holm-Bonferroni corrections to adjust for multiple comparisons.

To assess the capacity of DT turning measures to predict performance in civilian or military-relevant tasks, we will use Pearson correlation coefficients and linear regression models. Pearson correlation coefficients will compare the linear relationship between objective turning outcomes and the primary outcome of task completion time during the CAT and throughput during the SUP tasks within participants with mTBI, healthy control participants, and all participants together. To determine how changes in objective turning measures correspond to changes in functional performance, linear regression models will be built for each objective turning measure that was significantly associated with functional performance. The primary outcomes for the civilian and military-relevant tasks will be modeled as the dependent variable. To account for potential differences in performance between civilians and active-duty SMs, a group effect will be included as a covariate. Beta coefficients will be interpreted to identify the relative change in objective turning measures that are associated with changes equal in magnitude to 1 standard deviation of the healthy control participants' performance.

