#### Primary Outcome Measures—Responsiveness to Rehabilitation

To determine the responsiveness to rehabilitation, we will (1) determine the clinically important difference for objective turning outcomes and (2) compare the standardized response mean of each to rehabilitation to the minimum detectable change calculated in Phase I.

To determine the clinically important difference of turning outcomes, changes in objective turning outcomes will be anchored to the PGIC. Linear regression models will be fit to determine the differences in objective turning outcomes that are associated with a unit improvement in the patients' activity, symptoms, emotions, and overall quality of life, based on the PGIC.

To compare the effect of rehabilitation to the minimum detectable change, calculated from Phase 1, for each outcome, we will compute the mean difference between pre-rehabilitation and post-rehabilitation for each objective turning outcome. For each outcome, the ratio of the mean difference over minimum detectable change will be calculated. Ratios >1 will indicate that the mean difference due to rehabilitation was greater than normal variation between measurements, with larger ratios indicating larger effects due to rehabilitation.

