### Refinement of Tasks and Outcomes for Future Clinical Use

To reduce the number of tasks and outcomes, a variable selection procedure will be implemented. First, objective turning outcomes for each task will be ranked according to their (1) AUC in differentiating people with mTBI from healthy control subjects, (2) correlation with functional performance in the civilian-relevant task, (3) correlation with functional performance in the military-relevant task, and (4) ratio of mean effect of rehabilitation over minimum detectable change. Outcome–task combinations will then be ordered according to the sum of their ranks across these four categories, where a lower total is better. The outcome, and associated task, with the lowest total sum will be identified and put forward in future applications and clinical training tools. Additionally, a civilian-specific task/outcome combination will be identified by summing the ranks, but excluding the rank corresponding to the correlation with functional performance in the military-relevant task. A military-specific task/outcome combination will be identified similarly, but summing all ranks except the correlation with functional performance during the civilian-specific task.

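### Head turn symmetry is scored as a signed left-to-right ratio, so deficits on opposite sides offset each other in analyses that assume one direction of worse

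*Protocol article*

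**What the plan says.** In Table 1 of the protocol article, head turn symmetry is the last of five measures under "Other objective turning outcomes". Its description reads: "Assesses the ratio of left-to-right head-turn velocity". No absolute value, smaller-over-larger form or alignment to an affected side is given, and the eligibility criteria do not restrict the side of deficit.

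The article then uses the turning outcomes, symmetry included, in four places:

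- **Discrimination** (Phase 1, Statistical Analysis): the plan is to "construct receiver operating characteristic (ROC) curves using each objective turning outcome and clinical assessment of activity".
- **Prediction** (same section): "Pearson correlation coefficients will compare the linear relationship between objective turning outcomes and the primary outcome of task completion time" on the civilian route, and likewise throughput on the simulated patrol. Regression models follow only for measures that show a significant association.
- **Responsiveness** (Phase 2, Primary Outcome Measures): "we will compute the mean difference between pre-rehabilitation and post-rehabilitation for each objective turning outcome". This is then divided by the minimum detectable change.
- **Selection** (Refinement of Tasks and Outcomes for Future Clinical Use): "objective turning outcomes for each task will be ranked according to their (1) AUC in differentiating people with mTBI from healthy control subjects", the two correlations and the rehabilitation ratio. The ranks are summed.

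**The concern.** A signed ratio has its healthy value in the middle of its range, and abnormality lies on both sides of that value. An AUC on the raw marker credits one direction only. A Pearson coefficient measures a straight-line relation, whereas function would be expected to fall away on either side of the healthy value. A mean change lets a rise in one patient cancel a fall in another, even when both have recovered.

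The same coding therefore counts against symmetry in all four components of the rank sum. It may also keep symmetry out of the regression step, which a measure enters only through a significant correlation. A poor result could not be interpreted: it might mean no asymmetry, or asymmetry that cancelled. The rank sum decides which task and outcome go forward to clinical tools, so symmetry could be passed over because of how it was scored.

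**Working it through.** **1. The plan's own figures.** None is given for symmetry. The stated powers concern lumbar turning velocity, and both reproduce.

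- Goal 1: effect 0.65 × 1.20 = 0.78, 50 per group, two-sided 0.01. 0.78 × √(50/2) = 3.90, and Φ(3.90 − 2.576) = 0.907. The noncentral t gives 0.896. Stated: 90%.
- Goal 2: r = 0.362, N = 140. atanh(0.362) × √137 − 2.576 = 1.86, and Φ(1.86) = 0.969. Stated: 97%.

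Neither depends on the symmetry definition.

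**2. Even split, wider spread in mTBI (assumed).** Let log(L/R) be normal and centred on 0 in both groups, with k times the control SD in mTBI. By symmetry the raw AUC is 0.50 for every k. For the folded measure, P(|case| > |control|) = (2/π) × arctan(k).

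| k | Raw AUC | Folded AUC |
|---|---|---|
| 1.5 | 0.50 | 0.63 |
| 2 | 0.50 | 0.70 |
| 3 | 0.50 | 0.80 |

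**3. A shift to one side or the other (assumed).** Let the control log ratio be N(0, s) and the mTBI log ratio N(±a, s), with a share p shifted upwards. Put d = a/(s√2). Then:

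- raw AUC = pΦ(d) + (1 − p)(1 − Φ(d))
- folded AUC = Φ(d)² + (1 − Φ(d))², whatever p is

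For a = 0.3 and s = 0.10, d = 2.12 and Φ(d) = 0.983. The folded AUC is 0.983² + 0.017² = 0.97.

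| Side split | Raw AUC | Folded AUC |
|---|---|---|
| 50/50 | 0.50 | 0.97 |
| 60/40 | 0.60 | 0.97 |
| 70/30 | 0.69 | 0.97 |
| 80/20 | 0.79 | 0.97 |
| 100/0 | 0.98 | 0.97 |

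Simulation with 100,000 per group agrees. For smaller shifts at s = 0.10, the folded AUC is 0.64 (a = 0.1) and 0.86 (a = 0.2), and the 50/50 raw AUC stays at 0.50. The ordering can reverse. At a = 0.2 with all deficits on one side, raw is 0.92 against 0.86 folded. At a = 0.1 and 80/20, raw is 0.66 against 0.64.

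**4. Correlation.** In the same simulation, a function score was built to fall with |log(L/R)|, with noise equal to that quantity's SD. Its correlation with the folded measure is therefore about −0.71 by construction. With a 50/50 split, the raw ratio correlates −0.03 to −0.09 with the same score.

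**5. Mean change.** Take two illustrative patients who recover fully from equal and opposite asymmetry: 0.80 to 1.00, and 1.25 to 1.00. The mean raw change is (0.20 − 0.25)/2 = −0.025, close to nothing. On the folded scale each improves by ln(1.25) = 0.22.

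**The case against.** **The source is a condensed article.** The definition is a one-line table entry, and a fuller document may specify folding. That limits certainty about what will be run. However, the entry is a positive statement of a left-to-right ratio, not a gap, and as printed it does not fit the analyses printed beside it.

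**The side mix is unknown.** A reader might infer that symmetry cannot discriminate mTBI or predict function at all. The article does not support this. Complete loss needs an even split, and nothing in the text says the split is even. With uneven sides the measure is weakened, and if one side predominates the raw ratio can do as well as the folded one or better. This objection stands and sets the limit of the point.

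**Skew is a side issue.** AUC depends on ranks, so the skew of a ratio does not affect it, and a log without folding would leave the AUC unchanged. For modest asymmetry, 0.90 and 1.11 lie 0.10 and 0.11 from 1. The problem is direction, not skew.

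**The healthy centre may not be 1.** The Figure 1 caption describes fixed courses with mixed turn angles, and nothing shown says that left and right turns are matched. Folding about 1 could then use the wrong centre. This stands and is met in the fix.

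**The scope is small.** One of five non-primary turning outcomes is affected. This also stands.

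**Conclusion.** The point holds in a conditional form. The printed definition is signed, the printed analyses assume one direction, and deficits on both sides therefore offset. The measure loses all its value for discrimination, prediction and response if sides split evenly, and less as one side comes to predominate. With all deficits on one side nothing is lost. Under the assumed even split and SD ratios of 1.5 to 3, the raw AUC is 0.50 against 0.63 to 0.80 folded. The SD ratios, shifts and side shares are all assumptions, because the article reports none of them.

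The consequence is confined to one secondary candidate and its place in the rank sum. A reader might infer that the main findings or the sample size are in doubt. They are not: the primary outcome is peak lumbar turning speed, and both power statements concern lumbar turning velocity. The correction is still worth making before analysis, because otherwise a null result for symmetry could not be interpreted.

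**What to change.** In Table 1, define head turn symmetry as |log(left/right)|, so that larger always means more asymmetric. If course geometry makes the healthy ratio differ from 1, use |log(left/right) − the healthy-control median for that task|. Use this one form in the ROC, correlation, responsiveness, minimum detectable change and ranking steps.

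The change needs no new data or extra testing. It has two modest costs:

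- The folded index cannot be negative and has a noise floor. The minimum detectable change, taken as 1.96 × √2 times the within-subject error of a linear mixed model, therefore needs a check of the error distribution.
- If deficits turn out to lie mainly on one side, folding gives up some power (0.86 against 0.92 in AUC in the one-sided example at a = 0.2, s = 0.10). Describing the signed log ratio by group alongside the folded index would show whether this has happened.
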